## Abstract

**Background:**

Prehospital analgesia is often required after traumatic injury, currently morphine is the strongest parenteral analgesia routinely available for use by paramedics in the United Kingdom (UK) when treating patients with severe pain. This protocol describes a multi-centre, randomised, double blinded trial comparing the clinical and cost-effectiveness of ketamine and morphine for severe pain following acute traumatic injury.

**Methods:**

A two arm pragmatic, phase III trial working with two large NHS ambulance services, with an internal pilot. Participants will be randomised in equal numbers to either (1) morphine or (2) ketamine by IV/IO injection. We aim to recruit 446 participants over the age of 16 years old, with a self-reported pain score of 7 or above out of 10. Randomised participants will receive a maximum of 20 mg of morphine, or a maximum of 30 mg of ketamine, to manage their pain. The primary outcome will be the sum of pain intensity difference. Secondary outcomes measure the effectiveness of pain relief and overall patient experience from randomisation to arrival at hospital as well as monitoring the adverse events, resource use and cost-effectiveness outcomes.

**Discussion:**

The PACKMAN study is the first UK clinical trial addressing the clinical and cost-effectiveness of ketamine and morphine in treating acute severe pain from traumatic injury treated by NHS paramedics. The findings will inform future clinical practice and provide insights into the effectiveness of ketamine as a prehospital analgesia.

*Trial registration*: ISRCTN, ISRCTN14124474. Registered 22 October 2020, https://www.isrctn.com/ISRCTN14124474

## Background

At least 70% of Ambulance calls involve patients experiencing pain [1]. NHS Paramedics have a limited formulary to treat severe pain. Observational studies suggest that current treatments leave many patients with inadequate pain relief in the prehospital environment [2–6].

Effective management of acute pain is important for humanitarian reasons, for improving patient experience and reducing adverse long-term outcomes. In 2004 the World Health Organisation declared that effective management of pain is a universal human right. Poorly managed acute pain is associated with increased chronic pain. Studies indicate chronic pain is common following trauma with a reported incidence of 15–30%, increasing to 62% in patients suffering major trauma [7–9]. Poorly managed postoperative pain leads to persistent pain in 10–50% of common surgeries, and that pain is severe in about 2–10% of these patients [10]. Military personnel injured in recent conflicts demonstrate a link between acute pain management and subsequent depression or post-traumatic stress disorder (PTSD). Early aggressive pain management exerts a protective effect on the development of PTSD (OR 0.47 (95%CI 0.34–0.66) and depression (0.40 (95% CI 0.17–0.94) [11, 12]. Provision of early and effective analgesia has the potential to reduce the risk of developing chronic pain and adverse mental health outcomes post trauma, which may impact on patient’s long term quality of life [13, 14].

The Joint Royal Colleges Ambulance Liaison Committee (JRCALC) produce national clinical guidelines for NHS Ambulance Services. These guidelines suggest a stepwise approach to pain management according to the pain severity and availability of pre-hospital treatments for pain. The strongest parenteral analgesia routinely available for use by paramedics when treating patients with severe pain is morphine. Ketamine may be an ideal prehospital analgesic agent due to its rapid onset of action, superior analgesic properties and haemodynamic profile. The National Institute for Health and Care Excellence (NICE) has identified the need for a pragmatic, randomised trial to determine the clinical and cost effectiveness of ketamine against standard care (morphine) [15].

## Trial rationale

A barrier to effective pain treatment is the limited formulary available to paramedics. The most frequently used drug for moderate to severe pain outside a hospital is morphine [16]. Unfortunately morphine has several side effects (nausea, confusion, dizziness, drowsiness, respiratory depression, arrhythmia) that may limit its use [17–20]. This, and concerns about potential longer term dependence, limits effective use by clinicians [21]. Ketamine is perceived by many to be an ideal prehospital analgesic agent, favoured for its rapid onset of action, effective analgesia, good haemodynamic stability, and preservation of upper airway reflexes [22]. Ketamine has a distinct dose–response gradient in which small doses (< 0.5 mg/kg) provide an analgesic effect and large doses (> 2 mg/kg) an anaesthetic effect [23]. It exerts its effect by “disconnecting” the thalamocortical and limbic systems, effectively dissociating the central nervous system (CNS) from outside stimuli (e.g. pain, sight, sound) [24]. Ketamine also stimulates the sympathetic nervous system and moderately increases heart rate and blood pressure. Ketamine seldomly affects respiration; patients breathe spontaneously and maintain airway control [25]. Furthermore, there is evidence to indicate that perioperative ketamine analgesia may prevent hyperalgesia, reducing the risk of developing persistent post-operative pain [26, 27]. This suggests the potential for ketamine analgesia to be associated with a lower incidence of chronic pain post trauma.

Ketamine has a wide margin of safety. Serious adverse outcomes have not been reported even though overdoses of 5 to 100 times the intended dose have been inadvertently administered [28]. Due to its rapid onset and favourable side effect profile, ketamine is used in ambulance systems around the world [29–34] There are few definitive trials which compare its effectiveness, safety and cost-effectiveness.

## Methods and analysis

### Aim

The primary aim of this trial is to determine whether paramedic administered ketamine (intervention) or morphine (comparator) provides more effective pain relief for patients reporting severe pain following trauma, as measured by the Sum of Pain Intensity Difference (SPID), assessed using a 0–10 numeric rating scale.

Core trial information is presented in Table 1.

**Table 1 Tab1:** WHO trial registration data set

Data Category	Information
Primary registry and trial identifying number	ISRCTN14124474
Date of registration in primary registry	22/10/2020
Secondary identifying numbers	EudraCT number: 2020-000154-10 IRAS ID: 1003404 CPMS ID: 46938 REC reference: 20/WS/0126
Source of monetary or material support	National Institute for Health Research (NIHR)
Primary sponsor	University of Warwick
Secondary sponsor	N/A
Contact for public queries	[contact]
Contact for scientific queries	[contact]
Public title	PACKMaN
Scientific title	Paramedic Analgesia Comparing Ketamine and MorphiNe in trauma: PACKMaN
Countries of recruitment	UK
Health condition or problem studied	Acute severe pain from traumatic injury in adults
Interventions	Control: Pre-hospital morphine sulphate (0.10 mg/kg) Intervention: Pre-hopsital ketamine hydrochloride (0.15 mg/kg)
Key inclusion and exclusion criteria	*Inclusion*: Age ≥ 16 Patient reports a pain score ≥ 7/10 on a 0–10 numeric rating scale following acute traumatic injury Intravenous (IV) or intraosseous (IO) access obtained Determined by a paramedic to require IV morphine or equivalent *Exclusion*: Known or suspected pregnancy
Unable to articulate severity of pain using the 0–10 numeric rating scale	
Lack of capacity due to a reason other than pain IV/IO ketamine or opioid analgesia immediately prior to randomisation Known contraindication to ketamine or morphine as per the SmPC Patient declines participation Known prisoner	
Study type	Interventional, blinded, randomised, individual assignment. Phase III trial
Date of first enrolment	10-Nov-21
Target sample size	446
Current recruitment	362
Recruitment status	Recruiting
Primary outcome	Outcome name: Sum of pain intensity difference score Metric/method of measurement: using a 0–10 numerical rating scale Timepoint: From randomisation to arrival at hospital
Key secondary outcomes	Effectiveness of pain relief and overall patient experience from randomisation to arrival at hospital Incidence of side effects and adverse events Resource use Longer term outcomes
Ethics Review	Status: Approved Date of Approval: 01/09/2020 Committee: West of Scotland Research Ethics Committee Contact: [contact]

### Trial design and setting

This is a multi-centre, randomised controlled, double blinded trial comparing the clinical and cost-effectiveness of ketamine and morphine for severe pain following acute traumatic injury. It is a pragmatic, phase III trial working with two large NHS ambulance trusts with an internal pilot, aimed at mirroring existing practice of dealing with severe pain following acute traumatic injury. Participants will be followed up for 6 months. Adult patients (> = 16 years old) will be eligible for recruitment if they report severe pain following acute injury, in the pre-hospital environment and are determined by a paramedic to require parenteral morphine or equivalent.

The trial has been designed to determine if ketamine is superior to morphine as a prehospital analgesic. The prehospital phase ends once the patient arrives at hospital.

Randomisation will occur when the trial drug-pack is opened. The trial drug pack includes three ampoules of trial drug containing either ketamine of morphine. The ampoules of ketamine and morphine appear identical. The treating paramedic will not know which drug they are administering, hence the double blinding.

### Eligibility criteria

**Inclusion criteria**
Age ≥ 16Patient reports a pain score ≥ 7/10 on a 0–10 NRS following acute traumatic injuryIntravenous or intraosseous access obtainedDetermined by a paramedic to require IV morphine or equivalent

**Exclusion criteria**
Known or suspected pregnancyUnable to articulate severity of pain using the 0–10 NRSLack of capacity due to a reason other than painIntravenous (IV) or intraosseous (IO) ketamine or opioid analgesia immediately prior to randomisation*Known contraindication to either ketamine or morphine as per the published Summary of Product Characteristics (SmPC)Patient declines participationKnown prisoner

*The trial is a pragmatic one and mirrors real life practice, hence why some analgesics e.g. paracetamol are not a justification for exclusion. Administration of ketamine or morphine is likely to significantly bias results hence why these two analgesics are excluded. Immediately before, here, refers to administration by a by a clinician responder who has arrived on scene prior to the arrival of the trial trained paramedic.

### Patient recruitment and consent

The study aims to recruit 446 participants. Potential participants will be identified by the attending paramedic and if eligible will be enrolled into the trial.

Acute severe pain disrupts cognitive function and may impair mental capacity. Furthermore, patients with severe pain require urgent treatment to relieve pain for humanitarian reasons as well as to reduce the physiological stress caused by severe pain. It may therefore be impractical to obtain written informed consent prior to treatment from either the patient or a personal legal representative as to do so would delay treating the patient’s pain.

Before recruiting any patient to the trial, the paramedic will provide the patient with brief verbal information about the trial by reading predefined text from an aide memoire and advising the patient of their intention to enrol the patient into the trial. At this time, the paramedic will not be seeking informed written consent, but will provide the patient the opportunity to decline participation in the trial. Written informed consent will be obtained from the patient, or their legal representative, by research paramedics at the earliest opportunity, once the initial emergency has passed.

Ethics approval was granted on 01/09/2020 by West of Scotland REC 1.

### Allocation sequence and randomisation

The randomisation sequence will be provided by the Programming Team at the Warwick CTU. Randomisation will be achieved by way of specially prepared, sequentially numbered treatment packs containing identical ampoules of either ketamine (intervention) or morphine (comparator). The content of the drug packs will be determined from a randomisation list prepared by the study programmer. The blinded block randomisation system will look to ensure a ratio of 1:1 control: intervention. The balance between arms at each site is handled by the ordering system that ensures a pre specified number of paired packs are delivered to each site. The block size is determined by the number of drugs in any given site batch order. Distribution of trial drug packs by the trial drug manufacturer will ensure equal proportions of ketamine (intervention) and morphine (comparator) are distributed to each participating site. Allocation will be concealed from study personnel, ambulance staff and patients.

Numbered study drug packs in a pre-randomised sequence, will be carried by participating ambulance paramedics. Randomisation will be achieved by opening the pack. This avoids the need for any randomisation procedures before recruitment which could delay patient treatment.

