### Data analysis

The statistical analysis will follow the estimand framework [46]. Primary analysis will be by intention to treat. The primary outcome will be the SPID, a measure of the area under the curve of the pain score difference from baseline over time. The primary outcome will be analysed using a linear regression. Both unadjusted and adjusted (for important covariates) estimates and 95% confidence intervals for the treatment effect will be obtained. The adjusted estimates will form the basis for the primary analysis. Descriptive summaries of the outcomes will be presented as frequencies or means and medians. For the adjusted estimates, the covariates used will be age (< 60; ≥ 60 years), gender, weight and alternative parenteral IV paracetamol prior to randomisation (as a dichotomy split by yes or no). Age and gender have been chosen as covariates as these groups can experience pain differently, administration of IV paracetamol prior to randomisation is included as a covariate as it is an adjunctive treatment that may impact pain response. Weight is included as a covariate since different weight groups have different requirement for an adequate dose of IMP. For continuous secondary outcomes, analysis will be carried out in a similar way to the primary outcome. For categorical outcomes, logistic regression models will be used. Participant vital signs are recorded in a longitudinal format, for these outcomes we will use a mixed effect model.

Various intercurrent events have been identified for this trial, in line with the estimand framework [46], and approaches to dealing with these have been considered. For discontinuation of the allocated treatment and use of rescue analgesia, we will follow the treatment policy, where the data is analysed as observed. Compliance with administration of the trial drug as per the trial protocol will be monitored. If there is a noticeable degree of non-compliance, we will carry out a complier average casual effects (CACE) analysis [47, 48]. If sufficient data permits, sensitivity analysis will be conducted on a modified intention to treat population, excluding participants that were randomised but the drug was not given. Again, if sufficient data permits, participant deaths will be analysed using Pocock’s win ratio method, this allows death to be interpreted as a participant outcome and infer if the intervention is significantly better than the standard care having considered the clinical priority.

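### Allocation is balanced by site, but the primary adjusted model has no site or ambulance-service term, so its standard error is somewhat too large if site is related to SPID

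*Protocol article*

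**What the plan says.** **Allocation.** Under 'Allocation sequence and randomisation', site is a factor in the design. "The balance between arms at each site is handled by the ordering system", which sends a pre-specified number of paired packs to each one. "The block size is determined by the number of drugs in any given site batch order", so blocks are nested in site. Distribution by the manufacturer "will ensure equal proportions of ketamine (intervention) and morphine (comparator) are distributed to each participating site". 'Trial design and setting' describes the trial as "working with two large NHS ambulance trusts with an internal pilot". The article does not say whether a site is an ambulance service or a smaller unit.

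**Analysis.** Under 'Data analysis', "The primary outcome will be analysed using a linear regression", and "The adjusted estimates will form the basis for the primary analysis". The list is specific: "the covariates used will be age (< 60; ≥ 60 years), gender, weight and alternative parenteral IV paracetamol prior to randomisation". The section goes on to justify these covariates. Continuous secondary outcomes are to be handled in a similar way. No site or service term, random effect or stratified analysis of the primary outcome appears anywhere in the article.

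**The concern.** When allocation is balanced within a factor that predicts the outcome, the design removes that factor's variation from the treatment comparison. A model without the factor leaves the same variation in the residual, so the reported standard error is larger than the true sampling error of the estimate.

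A link between site and SPID is plausible here. Table 3 defines SPID as a time-weighted sum in hours, and the primary outcome runs from randomisation to hospital arrival. For the same sustained pain relief, a longer journey gives a larger SPID. Services or sites with different journey times would then differ in mean SPID. The article gives no journey times by site, so this is a reasoned expectation and not a documented fact.

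What is at stake is efficiency and agreement between design and analysis: wider intervals than necessary and some forgone power.

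**Working it through.** **1. The plan's own figure.** Inputs from 'Sample size': difference 1 NRS point, SD 3.0, power 90%, significance level 5% (taken as two-sided), non-response 15%.
- Per arm: 2 × [3.0 × (1.960 + 1.282) / 1]² = 189.1.
- Total after non-response: 2 × 189.1 / 0.85 = 445.0, or 446 as the next even number. The stated 446 is reproduced.
- The checks below use 190 per arm, 380 evaluable.

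**2. Effect of omitting site under exact balance.** Let f be the share of outcome variance that lies between sites, after the listed covariates. The documents do not give f; 2% to 15% is assumed. The model without site uses the full variance, while the true variance of the estimate is (1 − f) times that. Hence:
- ratio of model SE to true SE = 1/√(1 − f)
- type I error = 2 × [1 − Φ(1.96/√(1 − f))]

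| Assumed f | SE overstated by | Type I error | Coverage of 95% interval |
|---|---|---|---|
| 2% | 1.0% | 4.8% | 95.2% |
| 5% | 2.6% | 4.4% | 95.6% |
| 10% | 5.4% | 3.9% | 96.1% |
| 15% | 8.5% | 3.4% | 96.6% |

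For scale, with a total SD of 3.0 and 190 per arm, the interval half-width without site is 1.96 × 3 × √(2/190) = 0.603. At f = 10% a site term would bring it to 0.603 × √0.90 = 0.572.

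**3. What f means with two services.** For two equal services whose means differ by d, with residual SD 3, f = (d²/4)/(9 + d²/4), so d = 6 × √(f/(1 − f)). Shares of 2%, 5%, 10% and 15% need gaps of 0.86, 1.4, 2.0 and 2.5 points. Points here are on the scale of the sample size calculation. Because SPID is in point-hours, it is safer to read a 1-point gap as one third of the residual SD.

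**4. Simulation.** 10,000 runs per setting, 380 evaluable, two services, blocks of 10, residual SD 3, true effect 0 or 1 point.

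| Gap between services | Type I error without / with site term | Power without / with site term |
|---|---|---|
| 0 | 4.9% / 5.0% | 89.9% / 89.9% |
| 0.5 | 4.8% / 4.9% | 90.2% / 90.3% |
| 1 | 4.7% / 5.0% | 88.9% / 89.2% |
| 2 | 3.8% / 5.0% | 88.2% / 90.2% |
| 3 | 2.5% / 4.7% | 84.7% / 89.3% |

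Simulation error is about 0.2 percentage points for type I error, √(0.05 × 0.95/10,000), and 0.3 for power, √(0.9 × 0.1/10,000).

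**5. If balance is only partial.** Suppose half of the chance imbalance between sites remains among analysed patients (an assumption). The true variance is then (1 − f/2) times the model's. Type I error becomes 4.7% instead of 4.4% at f = 5%, and 4.4% instead of 3.9% at f = 10%.

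**The case against.** The strongest reply is that the omission does little harm. It makes the test conservative, so coverage is at or above 95%. The larger figures need large site effects: f = 10% corresponds to a 2-point gap between two services, twice the difference that the trial is designed to detect. This stands, and it limits the importance of the point.

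A second reply is that the design does not promise balance among analysed patients. It balances packs delivered. Packs are then carried by individual paramedics and opened as patients present, and some patients will not contribute data. This also stands, so the exact-balance figures are the most that the omission can cost at a given f.

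A third reply is that the analysis plan may add site. It may, but the article does not leave the covariates open: it names them and makes that adjusted estimate primary.

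Three stronger readings are tempting, and the documents do not support them:
- **The 5% level is invalid.** A reader might infer this from a type I error that differs from 5%. The departure is downwards only.
- **Site differences bias the treatment effect.** That would need imbalance within sites, which is the opposite of the condition that makes the intervals too wide. Chance imbalance adds noise that the model without site already allows for, and nothing in the documents puts a size on it.
- **The planned 90% power is lost.** That depends on whether the SD of 3.0 already contains variation between sites. If it does, power at f = 10% is 91.3% without the term and 92.9% with it, so a gain is forgone but 90% is kept. Power falls below 90% only if site variation comes on top of 3.0, as in the simulation.

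**Conclusion.** The point holds as a modest mismatch between design and analysis. That site is balanced by design and absent from the primary model is clear from the text. How much this matters is uncertain, because it rests on a between-site share that the documents do not give. Over the assumed range of 2% to 15%, the standard error is too large by at most 1.0% to 8.5%, and the test runs at a level between 4.8% and 3.4%. If services differ by about 1 point or less (f about 2.7%, SE overstated by about 1.4%), the effect is negligible. At 2 points or more it is worth recovering. The estimate is not biased by the omission and type I error is not inflated.

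**What to change.** Add the site unit used for pack ordering to the primary adjusted model: ambulance service as a fixed effect, or a random intercept for site if sites are many. Do the same in the linear models for continuous secondary outcomes that follow the primary analysis. The calculations here do not cover the logistic and mixed models, so whether to extend the term to them is a separate decision. Define site in the same place.

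With two services the cost is one degree of freedom and one line of text, and the sample size stays at 446. The article does not say that a pack number identifies its site, so the sponsor should confirm that the unit is recorded for every randomised participant. If site turns out to explain nothing, almost nothing is lost.

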### Blinding

The packaging and the labelling of the IMP packs will conceal which trial drug is being used therefore the patient, attending clinicians, research paramedics and trial administration team will be blinded. Only the statistician and the programming team will be able to link the trial drug pack number to the allocation of ketamine or morphine.

